### 2.2. Participants

The sample size was estimated using G*Power (version 3.1., University of Düsseldorf, City, Germany) [28]. A priori power analysis, based on the Wilcoxon signed-rank test, was conducted with an alpha level of 0.05, statistical power of 0.80, and a moderate effect size (Cohen’s d = 0.5). The analysis determined that 67 participants were required. To account for potential dropouts, the final sample size was set at 100 participants, with recruitment evenly distributed across four centers (approximately 25 participants per center). This design ensures robust data collection while allowing for comparative analysis of the interventions.

Participants for this study will be recruited through invitation letters distributed via four associations located across Spain. Eligibility criteria for inclusion in the study are as follows: (a) a confirmed diagnosis of ID arising from neurodevelopmental disorders or autism spectrum disorders; (b) classification of moderate or mild ID (based on a combination of IQ (Intellectual Quotient) scores and adaptive behavior), as defined by the criteria of the Spanish National Health System; and (c) Independent ambulatory ability.

The legal representatives or caregivers of potential participants will be responsible for consulting with the individuals, regarding their willingness to participate in the study and providing written consent on their behalf. Additionally, all participants will have the opportunity to express their own consent or assent regarding their involvement [29].

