### 2.3. Procedures

The registered sites will be randomly assigned to two groups using a random number table generated in Excel. The randomization process will be unrestricted, with no stratification or pairing of sites. To minimize selection bias, allocation concealment will be ensured by having an independent researcher generate the randomization sequence and store it in a secure file. Following the recruitment of the participating sites and the completion of the training period for monitors/caregivers, the randomization table will be unblinded, and the sites will be allocated to one of two groups. Preferably, the monitors/caregivers will be occupational therapists, physiotherapists, or social workers with specialized training in adapted exercise.

Group A will initially implement the NW program, followed by the Fit 5-Fitness Cards program. Conversely, Group B will undertake the programs in the reverse order. The random sequence will be generated by [name], while [name] will be responsible for informing the registered sites of the exercise sequence their members are required to follow.

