#### 2.4.2. Functionality

Dynamic Balance and Gait Speed: The “Timed Up and Go Test” (TUGT) will be employed, a reliable assessment tool for individuals with ID [31]. In a sample of 31 adults with ID, the TUG proved to be a feasible assessment tool, demonstrating excellent test–retest reliability (ICC: 0.90; 95% CI: 0.82–0.95) [32];Flexibility: The sit and reach test (SR) will be used to assess the impact of the program on the participants’ lower-body flexibility. For performing the SR, the participants will sit on the floor without shoes and with knees straight, and feet placed flat against the front-end panel of a standard SR box. Then, they will be asked to slowly reach forward as far as possible while placing the palms down along the measuring scale placed on the top of the box and to hold the position for approximately 2 s. The most distant point reached with the fingertips will be recorded (to the nearest centimeter). The best of two trials will be retained for analysis. The SR has demonstrated high reliability in a sample of 63 adolescents with ID (ICC = 0.97) [33] and has been previously used to assess fitness levels in adults with ID [34];Cardiorespiratory Fitness: Heart rate (HR) data will be collected using a Polar HR monitor (Polar Team Pro for iPad, version 1.0.1) during the tests. This method has been previously applied to individuals with ID [3].

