#### 2.4.5. Post-Intervention Average Weekly Physical Activity

Before the intervention begins, the participants and their parents will be asked to write the main physical activities (modality and duration) that they usually perform together in a typical week. Once the intervention ends (7 months after the start of the exercise program), a physical activity log will be given to the participants and their parents. They will be asked to register any type of physical activity (modality and duration) performed during a typical week of each month for the following six months.

Four NW poles will be given to the participants (two) and their parents (two) who complete the whole intervention. They will be encouraged to continue practicing NW by themselves for the next six months. Additionally, the registered offices that took part in the research will allow the use of the facilities in which the Fit 5-Fitness Cards and NW program took place at least two days per week, so that the participants and their parents could keep performing Fit 5-Fitness Cards and NW activities, also for the next six months.

Health-related PF, feasibility and QoL measurements will be carried out one week before the start of the training programs (To), once a week after the completion of the first stage (T1), one month later (T2), at the end of the second phase (T3), and six months later (T4). Record logs will be returned at T0 and T4. All the field-based tests and the questionnaire will be administered by the people in charge of the exercise intervention performed in each ID registered office.

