### 2.6. Statistical Analysis

Data will be reported as medians and interquartile ranges for non-normally distributed variables (checked with the Kolmogorov-Smirnoff test) or as means and standard deviations for normally distributed variables. Qualitative variables will be reported as n (%). The intra-cluster correlation coefficient and the cluster-specific effects will also be calculated. Inter-group quantitative variables will be compared, including the primary outcome, with an unpaired, two-tailed t test or the Mann–Whitney U test, as applicable. For inter-group dichotomous data comparison, the two-tailed chi-square tests will be used, with the Yates correction or Fisher’s exact test as appropriate. For repeated measures analysis, the two-way analysis of variance with the Bonferroni correction or the Friedman test, as appropriate, will be used. Comparison will be adjusted by cluster effect. Subgroup analysis of the primary outcome will include sex, age, BMI (normal, overweight and obese), level of physical activity (Inactive, Active), and level of ID (mild, moderate, severe). Multivariate regression models will adjust for confounders such as sex, age, BMI, physical activity, and ID level. Multicollinearity will be checked using the Variance Inflation Factor (VIF), with VIF > 5 indicating high collinearity [42]. Sensitivity analyses will assess robustness. Statistical significance will be set at a two-tailed *p*-value of less than 0.05. All analyses will be conducted using SPSS v24.0 software (IBM Corp., Armonk, NY, USA).

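### The unpaired test named for the primary outcome takes no pre-programme score and the named regression covariates omit it, so a Group A versus Group B comparison of post-programme scores carries chance baseline gaps and loses precision

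*Protocol article*

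**What the plan says.** Section 2.6 fixes the between-group test: "Inter-group quantitative variables will be compared, including the primary outcome, with an unpaired, two-tailed t test or the Mann–Whitney U test, as applicable". On covariates it says: "Multivariate regression models will adjust for confounders such as sex, age, BMI, physical activity, and ID level". The pre-programme value of the modelled outcome is not on that list, although the list is open-ended. The same section also plans a two-way analysis of variance or Friedman test for repeated measures, and an adjustment for cluster. It does not say which visits enter or how the adjustment is made.

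The baseline data exist. Section 2.4.5 states: "Health-related PF, feasibility and QoL measurements will be carried out one week before the start of the training programs (To", and it schedules the same measurements again at T2, a month after T1 and before the second programme.

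Section 2.2 plans 100 participants in four centres of about 25, and section 2.1 randomises centres 1:1. On balance, section 2.3 says: "The randomization process will be unrestricted, with no stratification or pairing of sites".

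Pre-programme scores are used explicitly only in the cost-effectiveness ratio of section 2.4.4. The incremental ratio there, which contrasts the two programmes, uses post-intervention scores alone.

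**The concern.** The baseline value is usually the strongest single predictor of a later score on the same scale. With two centres against two, and no stratification or pairing, randomisation cannot be relied on to balance baseline quality of life, Timed Up and Go or sit-and-reach. If the two groups are compared on raw post-programme scores, a group whose centres happen to start higher will appear to have responded better. The five named covariates remove only the part of that gap which they explain. Two things are at stake in such a comparison: how far the estimate reflects the starting gap rather than the programme, and precision given up from data the trial already collects.

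**Working it through.** **Inputs from the article.** Section 2.2: "A priori power analysis, based on the Wilcoxon signed-rank test, was conducted with an alpha level of 0.05, statistical power of 0.80"; target d = 0.5; 67 participants required, 100 planned, four centres of about 25. Section 2.6: "Statistical significance will be set at a two-tailed" level of 0.05. Section 2.1: two centres per group.

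**Assumed, because the article gives neither.** Intra-cluster correlation (ICC) 0.01 to 0.20; correlation rho between baseline and post-programme score 0.3 to 0.9. For the Timed Up and Go the article reports a measure "demonstrating excellent test–retest reliability (ICC: 0.90; 95% CI: 0.82–0.95", and 0.97 for sit-and-reach. These are test–retest figures, so at most upper guides to a three-month rho. Nothing comparable is given for quality of life.

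**The plan's own figure.** The signed-rank test at d = 0.5, two-sided 0.05, power 0.80 and a normal parent needs 35 participants, not 67. The two-sample Mann–Whitney test needs 67 per group. That is a separate matter and does not decide this point; I use 100 and 67 as stated.

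**Step 1: chance baseline gap, Group A minus Group B.** For 2 versus 2 centres of 25, in outcome SDs, SD = √(ICC + (1 − ICC)/25).

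| ICC | SD of gap | Share of d = 0.5 | P(gap above 0.25 SD, either way) |
|---|---|---|---|
| 0.01 | √(0.01 + 0.0396) = 0.22 | 45% | 26% |
| 0.05 | √(0.05 + 0.038) = 0.30 | 59% | 40% |
| 0.10 | √(0.10 + 0.036) = 0.37 | 74% | 50% |
| 0.20 | √(0.20 + 0.032) = 0.48 | 96% | 60% |

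**Step 2: does the gap reach the estimate?** In a simulated four-centre crossover with stable centre effects and no period or carryover effect, the Group A versus Group B difference in post-programme scores correlates 0.61 to 0.97 with the baseline gap (ICC 0.01 to 0.10, rho 0.5 to 0.9). It does.

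**Step 3: precision in that comparison.** Adjustment multiplies the variance by 1 − rho²: 0.75, 0.51 and 0.19 at rho 0.5, 0.7 and 0.9. Power comes from the noncentral t with d/√(1 − rho²) and one fewer degree of freedom, ignoring clustering:

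| Participants | Unadjusted | rho 0.3 | rho 0.5 | rho 0.7 |
|---|---|---|---|---|
| 50 v 50 | 70% | 74% | 82% | 93% |
| 34 v 33 | 52% | 56% | 64% | 81% |

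Allowing for clustering at ICC 0.05, the simulated standard error falls from 0.30 to 0.21 (rho 0.5) or 0.16 (rho 0.7) if centre effects are stable over time. If centre effects drift with the same rho, the fall is smaller: 0.30 × √0.75 = 0.26 and 0.30 × √0.51 = 0.21.

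**Step 4: absolute power with four centres.** The design effect is 1 + 24 × 0.05 = 2.2. With about 97 degrees of freedom, power would be 39% unadjusted and 49% at rho 0.5. A 2-versus-2 centre comparison has only about 2 degrees of freedom, which gives 17% and 21%.

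**Step 5: both periods compared by programme.** With complete data the correlation between the estimate and the baseline gap is about 0. With 33% lost before T3 (1 − 67/100, the allowance implied by section 2.2) it is 0.28 to 0.70. With complete data at ICC 0.05 and rho 0.7, entering each period's own baseline in the pooled unpaired comparison raises the standard error from about 0.08 to between 0.09 and 0.10. In a within-participant model, T2 minus T0 changes nothing when all visits are equally correlated.

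**The case against.** The strongest reply is that this is a crossover. Every centre delivers both programmes, so no centre has a programme of its own to be flattered by a good start, and stable differences cancel when programmes are compared over both periods. That stands, and step 5 confirms it for complete data. A reader might infer that baseline differences distort the programme effect whatever the analysis. The documents do not support that: it needs a period-1 or sequence-group comparison, or loss between periods. But section 2.6 does not commit to a within-participant contrast for the primary outcome. It names an unpaired test between groups.

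Second, a baseline covariate can do harm. In a pooled unpaired comparison with complete data it raises the standard error, and T2 may carry some effect of the first programme. This also stands, and it limits the remedy.

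Third, baseline is not wholly absent. A repeated-measures analysis that includes T0 would give a baseline-referenced group-by-time term, the covariate list is open, and the unpaired test might be meant for change scores. These are possibilities, not commitments, and none alters the test named for the primary outcome. The incremental cost-effectiveness ratio points towards raw post-programme scores. An article may leave detail to a fuller plan, but here the method is stated, and it is the stated method that is weak.

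Fourth, power figures that ignore clustering flatter the gain. That is right: on 2 degrees of freedom the gain at rho 0.5 is about 4 points.

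**Conclusion.** The concern holds in a limited form. The test fixed for the primary outcome and the covariates named for the regression leave out a pre-programme score that is collected. In a Group A versus Group B comparison of post-programme quality of life or fitness, the resulting gap has an SD of about 0.22 to 0.37 outcome SDs (ICC 0.01 to 0.10), or 45% to 74% of the target effect. The variance is 1/(1 − rho²) times what it need be, about a third more at rho 0.5. ICC and rho are assumptions. The relative loss is better supported than any absolute power, since four centres leave very few degrees of freedom.

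In a complete comparison by programme over both periods, the harm largely disappears. A reader might also extend the point to every outcome. That would be wrong: attrition, adherence, safety and cost have no meaningful baseline value, and the activity logs are returned only at T0 and T4. The larger, related weakness is the unpaired test itself in a trial justified by within-subject comparison. Correcting that would remove most of this problem.

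**What to change.** In section 2.6:

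1. For any between-group comparison of post-programme quality of life or fitness scores, replace the unadjusted test with a model that includes the T0 value of the same outcome. Keep the listed covariates and the cluster adjustment, and retain the t test or Mann–Whitney test as a sensitivity analysis.
2. For the programme contrast over both periods, state a within-participant model. If baselines are used there, enter T2 minus T0, not each period's own baseline in a pooled unpaired model.

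**Cost.** A sentence or two of text and one degree of freedom per outcome, with no new visits or participants. A rule is needed for participants without a baseline value. The within-participant model may gain little or nothing from the baselines if visits are equally correlated, and the text should acknowledge that T2 may carry residual effect of the first programme.

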To enhance exercise adherence, it is essential to identify activities that provide a clear and motivating structure. In this sense, the Fit 5-Fitness Cards program seems to be an interesting option. This program was created with the aim of promoting regular physical activity, nutrition and hydration among Special Olympic athletes. The Fitness Cards program provides a comprehensive set of exercises targeting four key fitness components: endurance, strength, flexibility, and balance. These exercises are structured across multiple levels, allowing individuals to progress at their own pace and adapt routines to their specific abilities [18]. This approach facilitates the involvement of both participants and their caregivers, fostering autonomy and promoting a healthier lifestyle. Previous research has demonstrated that the Fit 5-Fitness program is an effective and appealing intervention, yielding significant improvements in various health metrics, including reductions in blood pressure and resting heart rate [19]. Furthermore, both the Fit 5-Fitness Cards program and NW could positively contribute to reducing obesity in individuals with ID [19,20]. These findings are particularly critical given the high prevalence of obesity in individuals with ID and the pressing need for multifactorial strategies that encourage physical activity to mitigate this issue.

Despite the interest in physical activity approaches, there remains a gap in research regarding their effectiveness in enhancing functionality and QoL among individuals with ID. While scientific literature has confirmed the benefits of NW in various populations, such as healthy older adults [21], and individuals with metabolic pathologies [22], studies on its potential impact on ID are scarce. To the best of the authors’ knowledge, existing research has primarily focused on body composition, balance and gait parameters in individuals with Down syndrome [23,24]. The only known study examining the effects of NW in this population assessed its impact on body composition and physical fitness in 12 obese women with ID [25]. Therefore, further research is needed to explore the broader benefits of NW for individuals with ID.

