## 2. Materials and Methods

### 2.1. Study Design

This is a pilot study employing a crossover, cluster-randomized design with repeated measures. This design allows for a within-subject comparison, reducing inter-individual variability and increasing statistical efficiency compared to parallel-group trials, where each subject receives only one treatment [27]. Participating centers will be randomized in a 1:1 ratio into two groups. Two sequential interventions (NW program and Fit 5-Fitness Cards) will be conducted, separated by a 4-week washout period to mitigate potential carryover effects [27]. Following the washout period, the interventions will be repeated in reverse order, adhering strictly to the established protocol. A comprehensive outline of the design and procedures is presented in Figure 1.

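### No analysis of this two-period crossover names a period term, and the regression lists as confounders person-level factors that cannot confound the within-person programme contrast

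*Protocol article*

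**What the plan says.** All references are to the protocol article.

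- **Section 2.1** justifies the design by its paired nature: "This design allows for a within-subject comparison, reducing inter-individual variability". It adds: "Participating centers will be randomized in a 1:1 ratio into two groups".
- **Section 2.3** defines the orders: "Group A will initially implement the NW program, followed by the Fit 5-Fitness Cards program". Group B does the reverse. On the allocation of sites: "The randomization process will be unrestricted, with no stratification or pairing of sites".
- **Section 2.2** plans four centres of about 25 participants, 100 in all, against 67 stated as required before dropout.
- **Section 2.6** gives the adjustment set: "Multivariate regression models will adjust for confounders such as sex, age, BMI, physical activity, and ID level". It also plans unpaired tests between groups (primary outcome included), a two-way ANOVA or Friedman test for repeated measures without naming the factors, and a cluster adjustment. Neither period nor sequence appears.
- **Covariate timing:** section 2.6 does not say at which visit BMI or physical activity is taken. Section 2.4.5 has the activity logs returned at T0 and T4. The Introduction says that "both the Fit 5-Fitness Cards program and NW could positively contribute to reducing obesity in individuals with ID".

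**The concern.** A crossover removes everything that is fixed about a person. It does not remove what differs between the first and second treatment phases, such as season, practice at the tests, or a change in how caregivers rate. If the two orders have equal numbers, these differences cancel in the programme contrast. If they do not, part of the difference is read as a programme effect.

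Section 2.6 names the factors that the design already handles, calls them confounders, and does not name the one that it handles only under balance. An estimate reported as adjusted for confounding could then still carry a period bias, and nothing in the listed covariates would reduce it. A smaller issue is that the timing of BMI is open. A BMI measured after a programme could lie on the path from programme to outcome, and adjusting for it could remove part of the effect.

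**Working it through.** The plan gives no figure for a period effect, so there is none to reproduce. The size of the shift below is an assumption.

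**Step 1: what cancels.** Write a person's response as person level + period effect + programme effect + error. Let τ be the NW minus Fit 5 effect and π the period 2 minus period 1 shift. The within-person NW minus Fit 5 difference has expectation

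- Group A (NW first): τ − π
- Group B (NW second): τ + π

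The person level, and with it sex, age at entry, ID level and any T0 value, drops out of both lines. The period shift does not.

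**Step 2: bias without a period term.** Averaging over nA and nB people (N = nA + nB) gives τ + π(nB − nA)/N.

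| nA:nB | (nB − nA)/N | π = 0.2 | π = 0.3 | π = 0.5 |
|---|---|---|---|---|
| 50:50 | 0 | 0 | 0 | 0 |
| 55:45 | −0.10 | −0.02 | −0.03 | −0.05 |
| 60:40 | −0.20 | −0.04 | −0.06 | −0.10 |
| 75:25 | −0.50 | −0.10 | −0.15 | −0.25 |

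The sign reverses if Group B is the larger.

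**Step 3: how likely are unequal orders?** Section 2.3 describes allocation without restriction. If each of the four centres is assigned independently with probability 0.5:

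- 2:2 split: 6/16 = 37.5%
- 3:1 or 1:3 split: 8/16 = 50%
- 4:0 or 0:4 split: 2/16 = 12.5%

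If the 1:1 ratio in section 2.1 means that a 2:2 split is enforced, imbalance can still come from centre size or loss. For illustration, losing one centre of 25 leaves 50:25. That is 75 completers, still above the stated 67, and (25 − 50)/75 = −1/3 of the shift enters the contrast.

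**Step 4: simulation.** There were 1,000 simulated crossovers per split, with N = 100, true programme effect 0 and π = 0.3. Three person-level covariates predicted the outcome. Error SD was 0.7 per measurement, so the within-person difference has SD 0.7 × √2 = 0.99. There was no centre effect.

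| nA:nB | No covariates, no period | Person-level covariates, no period | Covariates and period | Rejection at nominal 5%, no period |
|---|---|---|---|---|
| 50:50 | 0.004 | 0.004 | 0.004 | 3.7% |
| 60:40 | −0.069 | −0.069 | −0.009 | 8.7% |
| 75:25 | −0.151 | −0.151 | −0.003 | 31.4% |

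The person-level covariates changed no estimate by more than 5 × 10⁻¹⁵. At 60:40 the period term moves the estimate by 0.060, which is 0.20 × 0.3 as in Step 2; the remaining −0.009 is simulation noise.

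**Step 5: covariate timing.** With logs returned only at T0 and T4, and the post-intervention log starting after the second phase, physical activity can enter analyses of T1 to T3 only as a baseline value. The open question of timing therefore concerns BMI.

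**The case against.** - **The target of the regression is not stated.** Section 2.6 also plans unpaired comparisons. In a comparison of Group A with Group B within one phase, person-level factors do not cancel, and with four centres they may differ by chance. Adjusting for them there is ordinary, and period does not bias that comparison. This stands. The point is confined to the within-person contrast, which is the contrast that section 2.1 gives as the reason for the design.
- **Period may be intended.** The covariates are introduced as examples, and the two-way ANOVA could have time as a factor. A reader might infer that the plan rules period out. The document does not support that; it leaves period unnamed.
- **Adjustment for a consequence of treatment.** A reader might infer that the plan adjusts for physical activity changed by the programmes. The log schedule does not allow that for T1 to T3. For BMI it is possible but nowhere stated. The same five variables define the subgroups, which suggests participant characteristics.
- **The bias may be small.** It is zero at equal numbers, and 0.06 units at 60:40 with π = 0.3. If change from a phase-specific baseline is analysed (T0 to T1, T2 to T3), a steady linear drift adds equally to both three-month phases and cancels. This stands in part: π is then the period difference in change, and season or a practice gain concentrated early would still contribute.
- **Period is not the only threat.** Carryover is another, and section 2.1 provides a washout for it.

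**Conclusion.** The point holds for the within-person programme contrast. The listed person-level factors cannot confound it, and the factor that can bias it under unequal orders is named in no analysis. The bias is (nB − nA)/N of the period shift: none at equal numbers, one fifth at 60:40, one half at a 3:1 centre split. An unequal centre split is more likely than not (62.5%) if centres are assigned independently.

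This rests on three assumptions: a period shift exists (its size is not in the document; 0.2 to 0.5 units is illustrative), allocation is as unrestricted as section 2.3 says, and no analysis includes period unless it is named. The simulated rejection rates apply to π = 0.3 and independent participants only.

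It would go too far to say that the covariates are wrong in every analysis or that the result will be biased. At T0 they do no harm and may improve the precision of an A-versus-B comparison or serve as effect modifiers. This is a correction worth making before analysis, not a fatal flaw.

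**What to change.** State the programme comparison in section 2.6 as a mixed model with programme and period as fixed effects and participant as a random effect. Keep centre, the randomized unit, as the cluster adjustment already promised. It should act on the within-person contrast, because a centre intercept alone cancels just as sex does. Fix BMI and physical activity at T0. Describe sex, age, ID level, BMI and physical activity as precision covariates or effect modifiers, not as confounders of this contrast.

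Costs:

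- A wording change and one degree of freedom. In an analysis of four centre-level differences, this takes the degrees of freedom from 3 to 2 and the two-sided 5% critical t from 3.18 to 4.30.
- Some precision when orders are unequal. For independent participants the variance rises by N²/(4·nA·nB): 10000/(4 × 60 × 40) = 1.04 at 60:40, and 10000/(4 × 75 × 25) = 1.33 at 75:25.

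A period term cannot rescue a 4:0 split, where programme and period coincide.
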